### Sample size

G*Power 3.1 software was used to calculate the sample size. Based on Sahin [37] et al., the effect size was set to 0.9, with α = 0.025 and β = 0.1. Two sets of comparisons will be conducted (the VR + rTMS group vs. the rTMS group and the rTMS group vs. the control group). Considering a potential dropout rate of 15%, a total of 147 children (49 in each group) will be enrolled in this study.

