## Methods

### Study design

This is a randomized, single-blind (evaluator), prospective clinical trial (protocol version 2.0, date: 2023.02.28). Participants will be randomly and equally divided into 3 groups: the VR + rTMS group, the rTMS group, and the control group. Two 4-week sessions of treatment will be provided to participants, separated by an interval of one week. Assessments will be performed at baseline (week 0) and after the intervention (week 9). This study will follow the Standard Protocol Items: Recommendations for Intervention Trials (SPIRIT) guidelines [32] (Fig. 1) and the Consolidated Standards of Reporting Trials (CONSORT) statement (http://www.consort-statement.org (Fig. 2) [33]. The study’s trial registration number is ChiCTR230069853.

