### Ethics

The procedures in this protocol are in accordance with the standards of the Declaration of Helsinki [34]. The trial will adhere to the study protocol. The private and personally identifiable information of the participants will be strictly protected. This study has been approved by the Xinhua Hospital Ethics Committee (Shanghai, China) [XHEC-C-2023-006-2]. Two sets of comparisons will be conducted (the VR + rTMS group vs. the rTMS group and the rTMS group vs. the control group). Considering a potential dropout rate of 15%, a total of 108 children (36 in each group) will be enrolled. Written informed consent to participate will be obtained from all study participants and in case of minor’s informed consent will be obtained from parents/legal guardian(s) before the children are randomly assigned to groups and can choose the desired treatments after the trial.

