### Random assignment and blinding

Random assignment will be performed based on the patient number and a random number sequence. The physiatrist in charge of patient recruitment will number patients according to the registration order. An independent researcher will generate a random number sequence (random seed: 16,264) through a website (www.randomization.com) and seal the allocation result in 108 sequentially numbered envelopes. Chief physiotherapists for the intervention will individually obtain the random allocation results to confirm the interventions. We will prepare a case report form for each participant to record evaluation results. Outcome measurements will be collected at baseline and after the intervention in a specialized venue by one experienced physician trained in basic and advanced courses for paediatric functional assessment. This assessor will be employed full time and will not participate in the design and group allocation of this study and will be unaware of the study objectives and the group allocation of patients; this assessor will not have access to the random allocation sequence. Moreover, he or she will be blinded during the entire process (including blinded to patient names, outpatient numbers, and other important information related to the identity of the patients) and will not be able to obtain relevant information on group allocation and intervention methods.

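### The enrolment target of 147 contradicts the 108 given twice elsewhere and does not follow from its own planning inputs

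*Protocol article*

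**What the plan says.** The protocol article gives the number of children in three places.

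- **Sample size:** "the effect size was set to 0.9, with α = 0.025 and β = 0.1", calculated in G*Power 3.1 for two pairwise comparisons. After the 15% dropout allowance, "a total of 147 children (49 in each group) will be enrolled in this study".
- **Ethics:** for the same two comparisons and the same 15% dropout, "a total of 108 children (36 in each group) will be enrolled".
- **Random assignment and blinding:** an independent researcher will "seal the allocation result in 108 sequentially numbered envelopes".

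Allocation is equal across the three groups (Study design). The between-group test is an independent-sample t test on change scores, with a rank test as fallback (Statistical analysis, Main analysis). The article does not say whether alpha is one- or two-sided, or how the dropout allowance was applied.

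**The concern.** Both totals are described as the number to be enrolled, and both already include the dropout allowance. They therefore cannot be read as an evaluable number and an enrolled number, and no other part of the article reconciles them.

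Three things depend on the answer. The first is when recruitment ends: with two published targets, stopping at 108 or going on to 147 could each be presented as planned. The second is the ethics approval, because the lower figure stands in the same section as the approval statement and the article does not say which total was approved. The third is the allocation list, which covers 108 children and so falls 39 short of 147.

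The stated power is also in question, because at most one of the two totals can match the stated inputs.

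**Working it through.** **Inputs**

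- Standardised difference d = 0.9, alpha = 0.025, power = 1 − 0.1 = 0.90 (Sample size).
- Two groups of equal size per comparison (Study design), compared by an independent-sample t test (Main analysis).
- Dropout 15% (Sample size and Ethics).
- Assumptions: the effect size is a difference between two means in standard deviation units. Sidedness is not stated, so both are shown.

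**Step 1. Try to reproduce 147 (49 per group)**

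The power of the two-sample t test with n per group comes from the noncentral t distribution with 2n − 2 degrees of freedom and noncentrality d × √(n/2). The smallest n with power of at least 0.90, divided by 1 − 0.15 and rounded up, gives:

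| Alpha 0.025 | Evaluable per group | Power at that n | Enrolled per group | Total |
|---|---|---|---|---|
| Two-sided | 32 | 0.901 | 32/0.85 = 37.6, so 38 | 114 |
| One-sided | 27 | 0.901 | 27/0.85 = 31.8, so 32 | 96 |

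Neither gives 49 per group. Replacing the t test by a rank test at alpha 0.025, with the least favourable relative efficiency (0.864), gives at most 44 per group (132).

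**Step 2. Power that 147 delivers at the stated inputs**

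49 × 0.85 = 41.65, so about 41 completers per group. At d = 0.9 the t test then has power 0.962 two-sided or 0.981 one-sided, against the stated 0.90.

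**Step 3. Try to reproduce 108 (36 per group)**

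The normal approximation is n = 2 × (z for alpha + z for power)² / d².

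- Two-sided: 2 × (2.241 + 1.282)² / 0.81 = 30.6, so 31 per group.
- Adding 15%: 31 × 1.15 = 35.65, so 36 per group and 108 in total.
- Dividing by 0.85 instead: 31/0.85 = 36.5, so 37 per group and 111 in total.

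So 108 can be reached from the stated inputs. The route is not the exact t calculation of Step 1, and adding 15% does not fully offset a 15% loss.

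**Step 4. Power that 108 delivers at the stated inputs**

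36 × 0.85 = 30.6, so 30 to 31 completers per group.

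| Completers per group | Two-sided | One-sided |
|---|---|---|
| 30 | 0.879 | 0.929 |
| 31 | 0.890 | 0.937 |

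**Step 5. Size of the conflict**

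147 − 108 = 39 children, and 39/108 = 36%. The prepared envelopes fall short of 147 by the same 39.

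**Step 6. An effect size that would give 147**

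With d = 0.8 and the other inputs unchanged, the two-sided t test needs 41 evaluable per group (power 0.899 at 40, 0.907 at 41). Then 41/0.85 = 48.2, so 49 per group and 147 in total.

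**The case against.** The best defence is that the trial has a coherent plan for 108 and that 147 is a slip in one place. The Ethics figure and the envelopes agree with each other, and 108 is close to what the inputs require. Most of this stands. It locates the likely inconsistency, but it does not remove it: the odd figure is in the one section whose purpose is to justify the number. Nor does the article allow a reader to conclude that 108 is the approved total.

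Four stronger readings are tempting, and the article does not support them.

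- *The inputs give neither total.* This is too strong for 108, which a two-sided normal approximation with 15% added reproduces exactly.
- *Recruiting 108 fails to deliver 90% power.* This depends on sidedness. If alpha is two-sided, the shortfall is 1 to 2 percentage points. If it is one-sided, there is none. An alpha of 0.025 fits 0.05 split over two comparisons, but the article does not say that this is its origin.
- *The last 39 children would have no concealed allocation.* The article describes 108 envelopes, but its section on study population and recruitment also has an independent researcher assigning by telephone. The text supports a shortfall of 39 prepared envelopes and no more.
- *The true planning effect was 0.8.* The match in Step 6 is exact, but 0.8 appears nowhere in the article, and 0.9 is attributed to a cited study. It is an inference that tells the sponsor where to look.

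**Conclusion.** The point holds as worded in the heading. The total of 147 conflicts with two other sections and exceeds what its own inputs need by 33 children (two-sided, 147 − 114) or 51 (one-sided, 147 − 96). At the stated effect size it gives about 96% or 98% power per comparison, not 90%. The total of 108 agrees with the envelopes and approximately with the inputs, at 88–89% power two-sided or 93–94% one-sided.

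The serious part is the undefined enrolment target, not a loss of power: at d = 0.9 either total gives about 88% or more. The contradiction between sections needs no assumption. The power figures assume a two-sample t test, a standardised mean difference of 0.9 and exactly 15% dropout in each group.

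**What to change.** Check which total the ethics committee approved, then give that one total in the Ethics, Random assignment and blinding, and Sample size sections. In the Sample size section, also state the sidedness of alpha and the formula used for dropout.

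- **If the total is 108:** correct the Sample size section to 108 (36 per group), and restate power at effect size 0.9 as about 88–89% (two-sided) or 93–94% (one-sided) with 30 to 31 completers per group.
- **If the total is 147:** correct the Ethics section to 147 (49 per group), prepare 147 allocations before recruitment starts and correct the envelope count. Restate power at effect size 0.9 as about 96% (two-sided) or 98% (one-sided). Change the effect size instead only if the sponsor's calculation record shows that another value was used. It should not be chosen to fit the total.

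The cost is a few lines of wording and, for 147, 39 further allocations. Nothing done to the children changes.

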### Intervention

The participants will receive 2 treatment sessions (4 weeks/session, 3 days/week). There will be a one-week interval between the 2 treatment sessions.

#### VR + rTMS group

Participants in the VR + rTMS group will receive VR therapy, rTMS, and routine rehabilitation. The interventions will be conducted in the following order: routine rehabilitation, VR therapy, and rTMS.

The virtual reality rehabilitation system (VRRS, Khymeia Group, Noventa Padovana, Italy) will be used to administer VR therapy. Each participant will be fully immersed in the virtual environment that can provide visual and acoustic feedback. Participants will be guided to perform active motions such as touching or grasping specific objects, balance control, lower limb movement, and hip flexion in specific situations for 40 min [38]. Before the start, therapists will adjust the difficulty and intensity according to the child’s motor function and responses to VR.

rTMS will be administered through a figure-eight coil connected to a Yiruide NS1000 stimulator (Yiruide Company Limited, Wuhan, China). The resting motor threshold (rMT) is defined as the stimulation intensity that induces a motor evoked potential of the contralateral abductor pollicis brevis that reaches 50 µV more than 5 times in 10 stimulations applied to the primary motor cortex (M1). The rMT will be measured in every child before each course of treatment. LF-rTMS (1 Hz) will be applied to the M1 for 20 min on the unaffected side. The stimulation intensity will be set at 90% rMT, with a total number of pulses of 1200 [39].

Routine rehabilitation consists of movement therapy and occupational therapy. The participants will receive 40 min of exercise training every day mainly on controlling the head, rolling over, sitting, crawling, standing, and walking. After movement therapy, participants will complete 20-minute occupational training tasks, mainly including upper limb function training, sensory integration therapy, and orthotics usage.

#### rTMS group

Both the routine rehabilitation treatment and TMS for children in the rTMS group will be the same as those of the VR + rTMS group.

#### Control group

The control group will receive the same routine rehabilitation regimen as the rTMS group, but a 20-minute sham stimulation will replace rTMS after routine rehabilitation therapy. A figure-eight advanced sham coil will be located on the unaffected side over the M1. The appearance, operation process, sound, and vibration sensation of the device during treatment will be the same as that during verum rTMS [40].

### Outcome measure

#### Primary outcome

The primary outcome will be assessed at baseline and after the intervention. Pain measured by the revised FLACC scale (R-FLACC) [41] will be the primary outcome. With this scale, the physiatrist will observe the child’s uncovered body and legs for at least five minutes, describing the child’s pain level from 5 dimensions (Face, Legs, Activity, Cry, Consolability) and then provide scores on a three-point scale (ranging from 0 to 2) for each dimension. Higher scores indicate a higher pain level. The total score of the R-FLACC will be analysed.

#### Secondary outcome

Secondary outcomes will be assessed at baseline and after the intervention.

The 66-item version of the Gross Motor Function Measure (GMFM-66) [42] and Fine Motor Function Measure (FMFM) [43] will be used to evaluate motor function. The GMFM-66 includes sixty-six items in five categories (lying and rolling; sitting; crawling and kneeling; standing; walking, running, and jumping). The FMFM includes sixty-one items in 5 dimensions. For each item, the physiatrist describes it through language or demonstration before the test. Each item is scored on a four-point scale ranging from 0 to 3. Children are given three chances to try to complete the test item, and the best score is recorded. Higher scores represent better motor function.

The Faces Pain Scale-Revised (FPS-R) [44] will also be used to measure pain. The FPS-R consists of 6 facial expressions representing pain intensity from 0 to 10. Physiatrists judge the severity of pain by observing facial expressions such as frowning, deepening of the nasolabial groove, and opening the mouth.

Balance function will be measured by the interactive balance system (IBS; Tetrax Inc., Ramat Gan, Israel) [45]. This test involves having children maintain stability in standing position in eight postures for 30s each (stand on the force platform with eyes open/closed, stand on the foot pad with eyes open/closed, turn the head left/right with eyes closed, and lean the head forwards/back 30° with eyes closed). The susceptors on the soles of the feet measure the pressure on different parts of the plantar surface during the test and output a balance score with a maximum of 100. Higher scores indicate worse balance function.

The Barthel index will be used to measure subjects’ activities of daily living [46]. This scale contains 10 items, with each item scored on a scale of 0–5, 0–10, or 0–15. The items include eating, dressing, going up and down stairs, stool control, urination control, toilet use, transfer, flat walking, bathing, and grooming. The children’s ability to perform these tasks is scored. A higher score (out of a maximum of 100 points) reflects better functional independence.

Quality of life will be assessed by the Chinese version of the CP Quality of Life scale for children (CPQOL-child) [47] and the Pediatric Quality of Life Inventory Measurement Model: Cerebral Palsy Module (PedsQL-CP) [48]. The CPQOL includes a parent questionnaire and a self-report questionnaire. The parent questionnaire is suitable for children with CP aged 4–12 years. The self-report questionnaire is designed for children with CP aged 9–12 years. The PedsQL-CP is suitable for evaluating the quality of life of children with cerebral palsy, with a parent questionnaire designed for children aged 2–18 years, and a self-report questionnaire designed for children aged 5–18 years. Children who meet the age requirement of these questionnaires at baseline will be asked to complete the survey before and after treatment. The total score for each scale will be calculated after completion of the assessment.

#### Safety

Before the start of treatment, we will record the children’s history of seizures, syncope, headache, cognitive deficits, and behavioural disorders in detail. For children with adequate cognitive ability, subjective evaluation of treatment tolerance will be used to evaluate safety during and after treatment on a scale of 1 to 10, where 1 is the least pleasant and 10 is the most pleasant. If the score is less than 5 points, this reflects poor treatment tolerance, and the treatment will be stopped. For children with cognitive deficits, physiotherapists will observe the child’s expression during each treatment. According to the FPS-R, treatment should stop when there is frowning or deepening of the nasolabial groove on children’s faces. If mild adverse events occur (fatigue, local discomfort, headache), the treatment will be paused, the event will be recorded, and the treatment intensity will be adjusted. If severe adverse events (e.g., seizure) occur, the treatment will be stopped, emergency treatment will be provided, and the condition will be reported to the research leader.

### Statistical analysis

#### Main analysis

The R-FLACC scores before and after the intervention will be compared to determine the therapeutic effects in the three groups. Subjects in randomly assigned groups with baseline measurements will be enrolled in the analysis of primary outcomes using the following method.

 [1] All indicators will be analysed as continuous variables.

 [2] Boxplots will be used to detect outliers, the S‒W test will be used to test distribution normality, and Levene’s test will be used to test the homogeneity of variance.

 [3] A paired-sample t test will be used to analyse the difference in outcomes with data conforming to a normal distribution and homogeneous variance before and after the intervention. The Wilcoxon signed-rank test will be used to examine the difference before and after intervention for outcome measures that do not conform to a normal distribution or exhibit heterogenous variance.

 [4] The difference between the outcome measures of each group before and after the intervention will be calculated. An independent-sample t test will be used to analyse the difference between the groups if the differences are normally distributed and exhibit homogeneous variance; otherwise, the Wilcoxon signed-rank test will be used.

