**Methods:**

This study protocol is for a randomized controlled trial consisting of 2 treatment sessions (3 days/week for 4 weeks in each session, with a 1-week interval between sessions). We will recruit children aged 3–10 years with unilateral spastic CP (Gross Motor Function Classification System level I or II). Participants will be randomly divided into 3 groups: the VR + rTMS group (immersive VR intervention, rTMS and routine rehabilitation therapy), rTMS group (rTMS and routine rehabilitation therapy), and control group (sham rTMS and routine rehabilitation therapy). VR therapy will involve a daily 40-minute movement training session in a fully immersive environment. rTMS will be applied at 1 Hz over the primary motor cortex for 20 min on the contralateral side. The stimulation intensity will be set at 90% of the resting motor threshold, with 1200 pulses applied. A daily 60-minute routine rehabilitation therapy session including motor training and training in activities of daily living will be administered to all participants. The primary outcome will be pain intensity, assessed by the Revised Face, Legs, Activity, Cry, and Consolability Scale (R-FLACC). The secondary outcomes will include motor development, evaluated by the 66-item version of the Gross Motor Function Measure (GMFM-66) and Fine Motor Function Measure (FMFM); balance capacity, measured by the interactive balance system; activities of daily living; and quality of life, measured by the Barthel index and the Chinese version of the Cerebral Palsy Quality of Life scale for Children (C-CP QOL-Child). Safety will be monitored, and adverse events will be recorded during and after treatment.

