#### Secondary analysis

Data will be divided into an intention-to-treat analysis set and a safety analysis set. The intention-to-treat set will include subjects who were randomly assigned to groups and completed the baseline measurement. Subjects who received at least one intervention and underwent one safety assessment will be allocated to the safety analysis set. The change in secondary outcomes from before to after the intervention will be compared to determine the therapeutic effects in three groups using the intention-to-treat set through the same analytical method as the main analysis. The safety analysis will include counting the number of adverse events and the number of patients who drop out because of unbearable adverse events.

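### The main analysis puts within-arm before/after tests ahead of the between-group test and does not say that the between-group test decides efficacy

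*Protocol article*

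**What the plan says.** The Main analysis section begins: "The R-FLACC scores before and after the intervention will be compared to determine the therapeutic effects in the three groups". Two of its numbered steps are tests of effect.

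- Step [3] is a within-arm test: "A paired-sample t test will be used to analyse the difference in outcomes with data conforming to a normal distribution and homogeneous variance", with the Wilcoxon signed-rank test when normality or equal variance fails.
- Step [4] is a between-arm test. First, "The difference between the outcome measures of each group before and after the intervention will be calculated"; then "An independent-sample t test will be used to analyse the difference between the groups if the differences are normally distributed" and the variances are homogeneous; "otherwise, the Wilcoxon signed-rank test will be used".

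The Secondary analysis section says that changes in the secondary outcomes "will be compared to determine the therapeutic effects in three groups", by the same method as the main analysis.

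Elsewhere the trial is framed as a comparison between arms. The Sample size section states "Two sets of comparisons will be conducted" and names them: VR + rTMS against rTMS, and rTMS against control. It gives α = 0.025 alongside. The Introduction hypothesises that the combination does better than rTMS alone.

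On shared care, the Abstract says that a routine session of motor training and "training in activities of daily living will be administered to all participants". The Control group section confirms the same routine regimen with sham stimulation. The exclusion criteria rule out children who had rehabilitation for CP symptoms in the past 6 months.

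**The concern.** A before/after change within one arm is not protected by randomisation. It combines any effect of rTMS or VR with everything else that happens to the children over the nine weeks:

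- Routine rehabilitation starts afresh in every arm, because recent rehabilitation is an exclusion. The Introduction itself describes physical and occupational therapy as possible basic treatments for pain control.
- Families are told that all three treatments are effective (Study population section), so expectancy can act in every arm, sham included.
- For the motor outcomes, children aged 3 to 10 years may develop over that time whatever they are given.

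The lead sentence links therapeutic effects to before/after comparison, and the within-arm test comes first. An analyst who follows the text could therefore report a significant paired test in an active arm as efficacy when the randomised contrast shows nothing. Reading significance in one arm and non-significance in another as a difference between arms would be the same mistake in another form.

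**Working it through.** **Which comparison the trial is sized for.** The stated inputs are effect size 0.9, α = 0.025 and power 0.90. Taking α as two-sided (the protocol does not say), the two-sample formula gives n = 2(2.241 + 1.282)² / 0.9² = 30.6, so 31 per group. Adding 15% gives 31 × 1.15 = 35.7, so 36 per group and 108 in total, the figure in the Ethics section. The sizing is thus that of a two-group contrast. The 147 in the Sample size section is not reproduced from these inputs. That conflict is a separate matter, and both totals serve here only as a range.

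**Evaluable children per arm.** 36 × 0.85 = 30.6, taken as 30. 49 × 0.85 = 41.65, taken as 41.

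**Assumption.** The protocol gives neither the expected sham-arm change nor the SD of change. Let every arm improve by the same standardised amount d_z (mean change divided by SD of change), with no rTMS or VR effect, and take d_z from 0 to 0.8. Change scores are treated as normal with equal variance.

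**Step [3], one arm.** The paired t test at two-sided 0.05 follows a noncentral t with n − 1 degrees of freedom and noncentrality d_z√n. For d_z = 0.5 this is 0.5 × √30 = 2.74 or 0.5 × √41 = 3.20. The protocol assigns no alpha to these tests, so 0.05 is assumed. With p the probability of significance in one arm, and arms independent:

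- at least one of three arms significant: 1 − (1 − p)³
- rTMS arm significant and sham arm not: p(1 − p)

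| d_z | n | p, one arm | Any of 3 arms | rTMS yes, sham no |
|---|---|---|---|---|
| 0 | 30 or 41 | 0.050 | 0.143 | 0.048 |
| 0.3 | 30 | 0.355 | 0.732 | 0.229 |
| 0.3 | 41 | 0.466 | 0.848 | 0.249 |
| 0.5 | 30 | 0.754 | 0.985 | 0.185 |
| 0.5 | 41 | 0.878 | 0.998 | 0.107 |
| 0.8 | 30 | 0.988 | >0.999 | 0.012 |
| 0.8 | 41 | 0.999 | >0.999 | 0.001 |

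A simulation of 10,000 three-arm trials per setting agrees (for example 0.734 and 0.225 in the last two columns at d_z = 0.3, n = 30).

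**Step [4], same simulated trials.** With the independent-sample t test at two-sided 0.025 per contrast, each contrast rejects in 2.2–2.8% of trials and at least one of the two in 4.4–4.8%, whatever the common improvement. This fits the bound 2 × 0.025 = 0.05. The shared change cancels in the difference between arms.

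**The fallback in step [4].** The signed-rank test needs paired observations. Children in two different arms are not paired, so the test cannot make this comparison. If change scores fail the normality or variance check, the plan as written has no valid between-group test, and step [3] is the only test of effect that can be run. R-FLACC is a sum of five items scored 0 to 2, in children who need only a history of pain, so non-normality is a realistic possibility.

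**The case against.** The strongest reply is that the randomised contrast is already in the plan. Step [4] computes change scores and compares them between groups, and the Sample size and Ethics sections name the two contrasts. The lead sentence can be read as an introduction to all the steps, and step [3] never says that its result is the therapeutic effect. The Secondary analysis wording can equally mean a comparison of changes across arms. Paired tests reported beside a between-group test are not in themselves an error. All of this stands, and it rules out the inference that the plan rests on within-arm tests alone.

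Other strong readings also fail:

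- **That the sham arm will show an effect.** This depends on a change that the protocol does not give. The chance in a single arm is 5% if there is no shared change.
- **That regression to the mean is assured.** Entry requires a history of pain, not a minimum R-FLACC score. The Introduction also reports that chronic pain stays the same (45%) or worsens (34%) between visits, which does not suggest large spontaneous improvement.
- **That the paired tests are three extra primary tests breaching the 0.025 level.** The protocol neither calls them primary tests of efficacy nor assigns them an alpha.

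The reply does not settle which step decides efficacy: the text is silent, and its opening and order favour the before/after comparison. It also leaves the unusable fallback in step [4].

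**Conclusion.** The point holds as a matter of precedence and wording. The main analysis gives within-arm tests the leading place, does not name the between-group contrast as the test of efficacy, and passes the same ambiguity to the secondary outcomes. The size depends on the assumed shared improvement. With no treatment effect, a given arm's paired test at 0.05 is significant in 5% of trials at no change, 36–47% at 0.3 SD and 75–88% at 0.5 SD, with 30–41 evaluable children per arm. The step [4] t test stays at or below about 5% for the two contrasts together. These figures assume normal change scores, equal improvement in all arms and a two-sided 0.025 per contrast. It should be corrected before analysis, since following the text can produce an efficacy claim that randomisation does not support.

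**What to change.** 1. Reword the opening of the Main analysis section so that efficacy is judged only by the between-group difference in R-FLACC change under step [4], in the two contrasts already planned (VR + rTMS against rTMS; rTMS against control), each at the 0.025 given in the Sample size section.
2. Make step [3] descriptive: mean change with a confidence interval for each arm, and no efficacy claim drawn from it.
3. In step [4], replace the signed-rank fallback with a rank-sum (Mann-Whitney) test on the change scores.
4. Bring the Secondary analysis section into line, so that secondary outcomes are also compared between arms and within-arm changes are only described.

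The cost is wording and the loss of the within-arm p-values. Design, data collection and sample size are unaffected.

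### The primary between-group comparison uses unadjusted change scores; adjusting for the baseline R-FLACC already collected would cost nothing and in large samples is never less precise

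*Protocol article*

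**What the plan says.** The primary outcome is the R-FLACC total, five dimensions each scored 0 to 2. On timing, the Primary outcome section states: "The primary outcome will be assessed at baseline and after the intervention". On the score used: "The total score of the R-FLACC will be analysed".

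The Main analysis section defines who is analysed: "Subjects in randomly assigned groups with baseline measurements will be enrolled in the analysis of primary outcomes using the following method". A baseline value therefore exists for every child in the analysis.

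Item [4] of that section then fixes the comparison between arms. It begins: "The difference between the outcome measures of each group before and after the intervention will be calculated". The test follows: "An independent-sample t test will be used to analyse the difference between the groups if the differences are normally distributed and exhibit homogeneous variance". The fallback is: "otherwise, the Wilcoxon signed-rank test will be used". No regression, analysis of covariance or baseline covariate appears anywhere in the article.

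The Secondary analysis section handles the other outcomes "through the same analytical method as the main analysis". The Sample size section gives the planning values: "the effect size was set to 0.9, with α = 0.025 and β = 0.1", with two pairwise comparisons and 15% dropout.

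**The concern.** Subtracting baseline from follow-up treats each extra point at baseline as exactly one extra point at week 9. If the true slope of week-9 score on baseline is not 1, the subtraction corrects by the wrong amount. The estimate then carries avoidable variance and shifts with any chance difference in baseline pain between arms. A model with baseline as covariate estimates the slope instead.

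A slope below 1 is plausible here. The score comes from one observation of at least five minutes, in children enrolled on a history of pain. The documents do not establish the slope, though.

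What is at stake is precision, and how far the estimate in this one trial depends on baseline imbalance. The type I error rate is not at stake. The article states this analysis outright, so it is not a detail left to an unseen analysis plan.

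**Working it through.** **Inputs from the protocol.** Effect size d = 0.9, alpha = 0.025 and power 0.90 (Sample size). Enrolment is 49 per group in Sample size and 36 per group in Ethics, both with 15% dropout. Evaluable children per arm are 49 × 0.85 = 41.65, taken as 41, or 36 × 0.85 = 30.6, taken as 30.

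**Assumptions not in the protocol.** The pre/post correlation r, equal SDs at the two visits, a two-sided test, and d expressed on the SD of change. The Sample size section does not say which SD d refers to.

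**The plan's own figure.** With d = 0.9, two-sided alpha 0.025 and 90% power, the noncentral t gives 32 evaluable per group, and 32/0.85 rounds up to 38. The normal approximation gives 31 and 37. Neither reproduces 49. The conflict between the two totals is a separate matter; both are carried forward and nothing below depends on which is right.

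**Variance per child.** With baseline SD s0 and week-9 SD s1:

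- change score: s0² + s1² − 2·r·s0·s1
- baseline-adjusted: s1²(1 − r²)
- difference: (s0 − r·s1)², which is never negative and is zero only when the slope r·s1/s0 equals 1

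With equal SDs the ratio is (1 − r²)/[2(1 − r)] = (1 + r)/2. The effect size equivalent for the adjusted analysis is 0.9/√[(1 + r)/2].

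| r | variance ratio | equivalent d | power, 30 per arm | power, 41 per arm |
|---|---|---|---|---|
| planned (change score) | 1 | 0.900 | 87.9% | 96.2% |
| 0.9 | 0.95 | 0.923 | 89.6% | 96.9% |
| 0.7 | 0.85 | 0.976 | 92.7% | 98.2% |
| 0.5 | 0.75 | 1.039 | 95.5% | 99.2% |
| 0.3 | 0.65 | 1.116 | 97.7% | 99.7% |

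Power is by noncentral t with 2n − 2 degrees of freedom. Charging the adjusted analysis one degree of freedom for the covariate changes power by less than 0.1 percentage point.

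**Simulation check.** 10,000 trials were run at 41 per arm with a true effect of −0.5 SD. At r = 0.3, 0.5 and 0.7 the mean estimates (change, then adjusted) were −0.496 and −0.497, −0.500 and −0.499, and −0.501 and −0.502. The variance ratios were 0.66, 0.75 and 0.85, as the formula predicts. Both methods target the same effect.

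**Unequal SDs.** For s1/s0 from 0.6 to 1.5 and r from 0.3 to 0.7, the ratio ran from 0.33 to 0.998 and never exceeded 1.

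**Chance imbalance.** With equal SDs, the two estimates within one trial differ by a random amount with SD (1 − r)√(2/n), in units of the outcome SD. From r = 0.7 to r = 0.3 this is about 0.07 to 0.15 at 41 per arm, and 0.08 to 0.18 at 30.

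**If d = 0.9 is on the raw SD.** At 30 per arm, power (change, then adjusted) is 73.9% and 90.9% at r = 0.3, 87.9% and 95.5% at r = 0.5, and 98.5% and 99.4% at r = 0.7.

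**The case against.** The strongest reply is that nothing here is invalid. Under randomisation the change-score t test is unbiased, so the point is one of efficiency. That is correct. A reader might infer that the planned analysis is biased, but the documents do not support that. Imbalance moves the estimate in a particular trial; it does not shift its expectation.

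Second, the slope is unknown. The protocol reports no SD, correlation or repeatability for R-FLACC. This stands, so the gain can only be given as a range. At 41 per arm, with d on the change-score SD, planned power already exceeds the 90% target.

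Third, a reader might expect the largest gains for GMFM-66, FMFM, balance, Barthel and quality of life, because children aged 3 to 10 differ widely at baseline. The reverse is more likely. Wide and stable differences between children raise r and push the slope towards 1, where change scores lose little: the ratio is 0.95 at r = 0.9.

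Fourth, R-FLACC is a bounded 0 to 10 score, so the rank branch may well be the one used. The formula and power figures above do not describe that branch. It is unadjusted too, however, so the absence of baseline adjustment applies to both branches. That branch also names a paired test for independent groups, which is a separate error.

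**Conclusion.** The point holds as a free improvement. Item [4] fixes an analysis that is valid but, in large samples, never more precise than the baseline-adjusted one, and less precise whenever the slope differs from 1. The baseline value is in hand for every child analysed.

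The size depends on assumptions. With equal SDs and r between 0.3 and 0.9, the variance reduction is 35% down to 5%. With d = 0.9 on the change-score SD, the power gain is about 2 to 10 percentage points at 30 per arm and about 1 to 3.5 points at 41 per arm. It would matter most if the smaller enrolment figure applies, where planned power falls just short of 90%.

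The existence of the improvement is well supported; its size is not known.

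**What to change.** Replace the between-group test in item [4], including its rank fallback, with a linear model of week-9 R-FLACC on arm with baseline R-FLACC as covariate. Report the two planned contrasts (VR + rTMS against rTMS, and rTMS against control), each at alpha 0.025 with a matching confidence interval.

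Use the same model for each secondary outcome with that outcome's own baseline, accepting that the gain may be small where scores are stable over nine weeks. Adding age and GMFCS level, both already recorded, is optional and not needed for the point.

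The cost is a change of analysis wording and one degree of freedom per model, with no new data, visits or children. Make the change before anyone sees outcome data by arm.
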